### Procedure and data collection

Data collection includes demographic information, clinical information, imaging information, and laboratory examinations. The details are shown in Table 2.

**Table 2 tab2:** Information collection.

Information collection	Content
Clinical information	Demographic information, health economics information, physical examination, etc.
Surgery information	Type of surgical treatment, blood information, hemostasis subjective difficulty score, etc.
Clinical score	mRS score, GCS, ICH score, GOS
Special examinations of MACCPE	Head CT, venous ultrasound of lower extremities, myocardial enzyme, thromboelastogram
Others laboratory examinations	Blood routine, biochemistry, coagulation function
Outpatient or phone review	Rebleeding event, MACCPE, survival condition

The procedure includes screening (Step 1), randomization and administration (Step 2), and outcome evaluation (Step 3; Figure 1; Table 3).

**Figure 1 fig1:**
[figure not shown]
The flowchart of study procedures.

**Table 3 tab3:** Study procedures.

	STUDY PROCEDURES						
	Screening			Treatment	Follow-up		
	Admission	Intraoperative	Within 72 h	At 3 days	10 ± 4 days	30 ± 5 days	90 ± 7 days
Randomization				X			
Start antiplatelet therapy				X			
Clinical information	X						
Clinic score	X					X	X
Surgery information		X					
Special examinations of MACCPE			X		X		X^*^
Others laboratory examinations			X		X		X^*^
Outpatient or phone review							X

* The examinations will be completed on outpatient.

#### Step 1: Screening and enrollment

As shown in Figure, patients will receive a primary screening before operation. The evaluation includes head computational tomography (CT), deep venous ultrasound, coagulation and myocardial enzyme examination. The patients with (1) re-hemorrhage or residual hematoma expansion, (2) deep vein thrombosis, and (3) abnormality in myocardial enzymes examination.

### Step 2: Randomization and administration

The patients will be randomized in a 1:1 manner to the early start group and the normal start group. After informed consent, all enrolled patients will be randomly grouped using an online randomization system (Churun Information Technology Co., Guangdong, China). The patients in early start group will receive aspirin 100 mg per day. The patients in normal start group will not receive antithrombotic therapy until 30 days after operation.

#### Step 3: Outcome evaluation

During hospital stay, patients will receive a series of special examinations of MACCPE at 10 ± 4 days after administration of aspirin, in order to identify whether there is an occurrence of MACCPE. If patients have a sudden unconsciousness, or suddenly or gradually worsening neurological states after administration of aspirin, a head CT examination will be conducted immediately to identify whether there is an occurrence of re-hemorrhage. If the patient occurs ischemic events, the antiplatelet or anticoagulation therapy will be added to the patient based on the specific condition. These patients meet the endpoint when ischemic events occur, so they will not be excluded from this study.

Patients will be regularly followed up at 30 and 90 days. To the patient who did not discharge in 30 days, we would assess the clinic score at the bedside. To the discharged patient, we assess the clinic score *via* outpatient or phone review. At 90 days, if the patient could not complete the follow-up examination in the medical centers involved to the study, they will be required to complete the relative examinations in the local hospitals. Our investigators will ask patients’ family members to upload the follow-up data and assess the quality of these data. If these data are out of required quality and more details could not be got, the patients will be considered as the patients withdrawing from the follow-up (Figure 2).

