## Materials and methods

### Study design

This study is a multicenter, prospective, randomized, open-label, blinded-endpoint trial, which begins in May 2021, and is scheduled to be completed by May 2023. After operation, sSICH patients with high risk of ischemic events will be randomized in a 1:1 manner to early start group (start antiplatelet therapy at postoperative 3 days) and normal start group (start antiplatelet therapy at postoperative 30 days). The primary efficacy endpoint is the incident of MACCPE, and safety endpoint is the incident of re-hemorrhage. This randomized controlled trial (RCT) will follow the Consolidated Standards of Reporting Trials (CONSORT) guidelines.

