### Endpoints and relative definitions

The primary efficacy endpoint is the incidence of MACCPE after operation. The MACCPE event is identified when patients suffer from a new cerebral infarct outside the surgical area, enlarging cerebral infarction area, new-onset TIA, more frequent TIA, new-onset myocardial infarction, reperfusion therapy for original myocardial infarction, pulmonary embolism, or deep venous thrombosis.

The other outcomes included: (1) the 3-month mortality after surgery; (2) in-hospital mortality; (3) 30- and 90-day neurological function after operation, which is assessed using the modified Rankin scale (van Swieten et al., 1988) (mRS) or Glasgow outcome scale (Jennett and Bond, 1975; GOS).

The safety endpoint is the incidence of hemorrhagic complications during antiplatelet therapy, i.e., the radiological re-hemorrhage of the operative region (comparing with the preoperative or postoperative first images) or new occurrence of intracerebral hemorrhage, subdural hemorrhage, subarachnoid hemorrhage or intraventricular hemorrhage.

For the cerebral infarcts, immediate CT (due to sudden or continuously deteriorating neurological state) and regular follow-up CT (postoperative 7 ± 5 days, postoperative 90 ± 10 days) will screen new hypodense lesions. If new hypodense lesions are found, an MRI will be used to determine the lesions. New cerebral infarcts outside the surgical area were defined as new hypodense lesions on T2-weighted MRI, which are visible in at least two continuous views. Enlarging infarctions were defined as an increase in a previously existing area of T2-weighted signal hyperintensity of at least 3 mm in one dimension (Vendt et al., 2009).

Transient ischemic attack (TIA) was defined as a transient episode (duration of symptoms < 24 h) of neurological dysfunction caused by focal brain, spinal cord, or retinal ischemia without showing acute infarction on CT images. The primary endpoint was met if patients presented with new-onset TIA or more frequent TIA.

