Myocardial infarction is defined as myocardial necrosis in a clinical setting consistent with myocardial ischemia. These conditions can be satisfied by a rise of cardiac biomarkers (preferably cardiac troponin [cTn]) plus at least one of the following: (1) symptoms of cardiovascular ischemia; (2) ECG changes indicative of new ischemia (significant ST/T changes or left bundle branch block); (3) development of pathologic Q waves; (4) imaging evidence of new loss of myocardium or new regional wall motion abnormality; (5) angiography or autopsy evidence of intracoronary thrombus.

The patients who had CT pulmonary angiography or autopsy evidence of pulmonary embolism were defined as pulmonary embolism. For the patients who had no evidence, if they fulfilled the criteria described below, they were also defined as pulmonary embolism. The criteria include (1) clinical manifestations of pulmonary embolism: cough, chest pain, hemoptysis, dyspnea, etc.; (2) Wells score > 4; (3) blood tests showed high D-dimer levels, high Troponin levels, low blood oxygen saturation, high alveolar-arterial (A-a) oxygen partial pressure; (4) venous ultrasound of lower extremities showed deep vein thrombosis.

Deep venous thrombosis was defined as the follow-up venous ultrasound of lower extremities that showed hyperechoic or mixed echogenicity in deep venous. Deep veins mainly include femoral vein, popliteal vein, anterior tibial vein, posterior tibial vein, fibular vein, and iliac vein.

Re-hemorrhage of the operative region was defined as new high-density focal lesions in the surgical area or original hematoma enlargement comparing with the preoperative CT and first postoperative CT. Postoperative subdural hemorrhage, subarachnoid hemorrhage, and intraventricular hemorrhage were also confirmed by postoperative CT.

Two investigators will identify blinded to the patient information assesses the occurrence of MACCPE and rehemorrhage events on 10 ± 4 and 90 ± 14 days post-surgery. mRS scores, GCS, and GOS will be assessed on 30 days/discharge and 90 ± 14 days post-surgery.

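### The clock and windows for the MACCPE examinations contradict each other, and one of the stated clocks, read literally, would time the first look differently in the two arms

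*Protocol article*

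**What the plan says.** Four places in the protocol article set the timing.

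- **Step 3: Outcome evaluation** schedules, during the hospital stay and without naming an arm, a set of special examinations at 10 ± 4 "days after administration of aspirin, in order to identify whether there is an occurrence of MACCPE".
- **Endpoints and relative definitions**, on the blinded assessors: "assesses the occurrence of MACCPE and rehemorrhage events on 10 ± 4 and 90 ± 14 days post-surgery".
- **The same section**, on cerebral infarcts: "regular follow-up CT (postoperative 7 ± 5 days, postoperative 90 ± 10 days) will screen new hypodense lesions".
- **Table 3** has one 10 ± 4 day column for these examinations, placed before the 30 ± 5 day column and not split by arm, and a last column at 90 ± 7 days. It does not say what the days are counted from.

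The start of treatment depends on the arm. Study design has "early start group (start antiplatelet therapy at postoperative 3 days" and "normal start group (start antiplatelet therapy at postoperative 30 days". Step 2 adds "The patients in normal start group will not receive antithrombotic therapy until 30 days after operation". It names an agent for one arm only: "The patients in early start group will receive aspirin 100 mg per day".

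Table 2 lists head CT, lower-limb venous ultrasound, myocardial enzymes and thromboelastogram as the special examinations. The infarct-screening CT and the head CT in this set are thus the same kind of test under different windows.

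**The concern.** Part of the primary endpoint is found only by looking. Deep venous thrombosis is defined by follow-up ultrasound, and new infarcts are screened by scheduled CT. For such components the date of the look helps decide whether and when an event is counted. If the look is tied to the start of aspirin, it is tied to the randomised arm. Blinded reading cannot correct for when a scan was taken, and in an open-label trial the sites know which arm-dependent date to apply.

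The Discussion says MACCPE begins about postoperative day 4 and peaks on day 7. A first scheduled look more than five weeks after surgery in one arm would therefore be far from the period of interest. Cox models are planned for the primary endpoint in subgroups, so detection dates matter as well as final counts.

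**Working it through.** The plan gives no figure to reproduce here. The check is date arithmetic, followed by an illustration.

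**Step 1. Each rule as postoperative days.** Aspirin-anchored window = start day + (10 ± 4). Early start: 3 + 6 to 3 + 14 = days 9–17, centre 13. Normal start: 30 + 6 to 30 + 14 = days 36–44, centre 40. The centres differ by 40 − 13 = 27 days, which is the gap between the start days (30 − 3). The windows do not overlap.

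| Place | Clock | Early look | Late look |
|---|---|---|---|
| Step 3 | aspirin | 9–17 (early start); 36–44, or undefined without an aspirin date (normal start) | 90 days, no window given |
| Endpoints, blinded assessment | surgery | 6–14 | 76–104 |
| Endpoints, screening CT | surgery | 2–12 | 80–100 |
| Table 3 | not stated | 6–14 if from surgery | 83–97 if from surgery |

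**Step 2. What differs by arm.** Only the Step 3 rule can. The other rows conflict with each other, but equally for both arms.

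**Step 3. Illustration of the literal Step 3 reading, with no treatment effect.** From the document: event rate 10.8% (Sample size), onset from day 4 with mode at day 7 (Discussion). Assumed, and not in the document: the share of events found only by screening, how long a lesion stays detectable, and CT and ultrasound both following the aspirin clock. The first look is centred on day 13 (early) or day 40 (normal), each ± 4 days, and the last on day 90 ± 7 in both arms. Detected events, normal start vs early start:

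| Assumption | By day 30 | By the 90-day look |
|---|---|---|
| 25% screen-only, lesions permanent | 8.1% vs 10.2% | 10.8% vs 10.8% |
| 50% screen-only, mean persistence 60 days | 5.4% vs 9.2% | 8.7% vs 9.6% |
| 75% screen-only, mean persistence 30 days | 2.7% vs 8.0% | 5.7% vs 8.2% |

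The false gap by day 30 is 2.1, 3.8 and 5.3 percentage points. By the 90-day look it is 0, 0.9 and 2.5 points. Where there is a gap, normal start shows fewer events, so it works against early start.

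**Step 4. After the fix.** With both arms examined at 10 ± 4 days from surgery, the gap in timing is 0 days. In the 50%, 60-day scenario, detection by day 30 is 8.2% vs 8.2%.

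**The case against.** The strongest reply is that a common schedule is plainly intended. The blinded assessment and the screening CT are both counted from surgery. Table 3 has a single, unsplit 10 ± 4 day column ahead of day 30 and no examination column at days 36–44. Step 3 speaks of the hospital stay, which fits poorly with those days. Aspirin is named only for the early arm, so the phrase may be shorthand for the day-3 treatment point. Step 3 would then give days 9–17 in both arms against 6–14 elsewhere: three days apart, overlapping, and equal by arm.

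Most of this stands. A reader might infer that primary events are in fact looked for at different times in the two arms. The document does not support that as a statement of fact. It follows only if Step 3 is applied literally to normal start. The reply does not remove the contradiction, however. Table 3 states no anchor, and the follow-up figure is not available to settle it. A site that used the aspirin date where one exists and the surgery date otherwise would still look three days later in early start (9–17 vs 6–14).

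Three further inferences go too far.

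- **The late windows.** They conflict between sections, not between arms, and cannot cause differential ascertainment.
- **The day-2 opening of the CT window.** Patient selection already bars from randomisation anyone with a new infarct, hemorrhage, venous thromboembolism or acute coronary syndrome within 3 days of operation. A positive early scan leads to exclusion rather than a counted event, and the overlap precedes randomisation in both arms.
- **That two or three missed control events would change the result.** Reading the planned 5% reduction as percentage points, 125 × 0.108 ≈ 14 and 125 × 0.058 ≈ 7 events. The chi-square p is 0.11. Removing two or three control events gives 12 vs 7 (p = 0.23) or 11 vs 7 (p = 0.33). None is significant, so the conclusion at the expected counts is unchanged.

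**Conclusion.** The contradiction is real. The article contains two clocks (aspirin and surgery) plus a table with no stated clock, two early windows (7 ± 5 and 10 ± 4 days) and three late windows (± 7, ± 10 and ± 14 days) for overlapping examinations.

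The arm-dependent look is conditional. If Step 3 were followed as written, the first scheduled look would be 27 days apart between arms, or undefined in normal start. This would affect ultrasound-detected thrombosis, and silent infarcts only if the CT follows the same clock rather than its own postoperative one. Bias would tend to run against early start. It would be smaller by the common 90-day look, and none would remain in the final counts if lesions stay detectable until then. The sizes in the illustration rest on assumed screening shares and persistence times and show direction and rough scale only.

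**What to change.** Reconcile Step 3, both timing statements in Endpoints and relative definitions, and Table 3:

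1. Count all scheduled MACCPE examinations from one date, operation or randomisation, identically in both arms, and state that anchor in Table 3.
2. Remove aspirin administration as the anchor for the scheduled examinations in Step 3.
3. State one early window that opens after randomisation and covers CT, ultrasound and enzymes together. The endpoint section's 10 ± 4 days from surgery would serve, since it opens on day 6.
4. State one 90-day window and use it throughout.

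The cost is protocol wording and notice to the sites. The examinations are already planned, none is added, and no treatment changes.

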**Figure 2 fig2:**
[figure not shown]
Follow-up plan.

During observation, investigators will detailly record the following events:

MACCPE (the occurrence time, special treatment and radiological data).Mortality (the occurrence time and cause of death).Neurological function outcome, which is evaluated by the mRS, GCS, and GOS.Intracranial re-hemorrhage or intracranial bleeding potentially related to aspirin (the occurrence time, treatment, radiological data and cause of bleeding).Regular follow-up head CT.

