### Monitoring the effectiveness of antiplatelet therapy

Before and after aspirin administration, we will assess the platelet function. The platelet function will be assessed using the thromboelastogram (TEG). All parameters, including maximum amplitude (MA), citric acid kaolin (CK), reptilase (A), aspirin (AA), are recorded through standard tracing. Based on MA, the rate of platelet function inhibited by aspirin (AA%) was calculated using the formula as shown below:

$$AA\%=\frac{MA\left(CK\right)-MA\left(AA\right)}{MA\left(CK\right)-MA\left(A\right)}$$

For patients in the early start group, the platelet function will be detected before aspirin administration and 7 days after administration. AA% > 50 is defined as the good response to aspirin. Moreover, for the patients in the normal start group, because they do not receive any antiplatelet therapy, the platelet function assessment do not need to perform for these patients.

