### Quality control of the research

To avoid participant bias and ensure a sufficient source of operated sSICH patients, we will enroll appropriate centers according to follow standards: (1) the medical centers cover at least two communities or work as a referral unit for hemorrhagic stroke; (2) the center can conduct various treatments for sSICH and can fully represent the diagnosis and treatment of sSICH at a national level; (3) the medical center treats at least 50 sSICH patients annually by surgical methods; (4) the center can complete all examinations which are required in the study. Finally, nine medical centers encounter our standards and participate in this study. This study will conduct in nine regional neurosurgical centers simultaneously.

In this study, operation decision is made based on the consensus of neurosurgeons and patient family, according to clinical guideline. The operation is performed by a senior neurosurgeon, working as a neurosurgeon for more than 10 years. After operation, all of the patients would receive standardized care according to the guidelines. Before and after operation, patient will receive blood pressure management, and the target blood pressure is <140/90 mmHg.

At statistical stage, we will review all postoperative treatments and further exclude: (1) the patients receiving non-indicated platelet transfusion or anticoagulation treatment; (2) the patients whose the postoperative blood pressure are abnormal even receiving special treatment; (3) the patients suffering from an abnormal change of blood cells, abnormal hypercoagulation or disseminated intravascular coagulation.

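### The safety endpoint counts bleeds only while on antiplatelet drugs, which does not fit the rescue rule or an untreated control arm, so the two arms are counted over different windows

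*Protocol article*

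**What the plan says.** All references are to the protocol article.

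- **Endpoints and relative definitions:** "The safety endpoint is the incidence of hemorrhagic complications during antiplatelet therapy". The list that follows covers re-bleeding in the operated region and new intracerebral, subdural, subarachnoid or intraventricular bleeding.
- **Abstract and Study design:** the safety endpoint is simply re-hemorrhage, with no condition on treatment.
- **Step 3: Outcome evaluation:** "If the patient occurs ischemic events, the antiplatelet or anticoagulation therapy will be added to the patient based on the specific condition". Nothing confines this to one arm. It continues: "These patients meet the endpoint when ischemic events occur, so they will not be excluded from this study".
- **Step 2: Randomization and administration:** "The patients in normal start group will not receive antithrombotic therapy until 30 days after operation". No exception for rescue is stated.
- **Monitoring the effectiveness of antiplatelet therapy:** platelet function is not tested in the normal-start group "because they do not receive any antiplatelet therapy".
- **Quality control of the research:** the later exclusions name "the patients receiving non-indicated platelet transfusion or anticoagulation treatment". Patients on an indicated rescue drug are therefore not removed on that ground.
- **Events to be recorded (list after Figure 2):** "MACCPE (the occurrence time, special treatment and radiological data", and "Intracranial re-hemorrhage or intracranial bleeding potentially related to aspirin (the occurrence time, treatment, radiological data and cause of bleeding".

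**The concern.** A safety comparison needs the same event, counted over the same period, in both arms. Here the endpoint definition makes counting depend on whether the patient is on antiplatelet treatment when the bleed occurs. That condition is met in the early-start arm from about day 3. In the normal-start arm it is normally met only from day 30, or earlier if a rescue antiplatelet drug is given.

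Rescue adds a second problem. MACCPE includes deep venous thrombosis and pulmonary embolism as well as arterial events, so both antiplatelet and anticoagulant rescue can be expected. Two control patients with the same bleed on the same day are then counted differently according to which class of drug the treating team chose.

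The Discussion says the trial asks whether early aspirin prevents MACCPE without increasing re-hemorrhage. If the bleeding count means different things in the two arms, that second half cannot be read from the result.

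**Working it through.** **1. The literal count, state by state**

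| Patient state at the bleed | On an antiplatelet? | Counted under the endpoint definition? |
|---|---|---|
| Early start, on aspirin, from day 3 | Yes | Yes |
| Early start, rescue drug added to aspirin | Yes | Yes, whatever the rescue class |
| Normal start, before day 30, no rescue | No | No |
| Normal start, before day 30, rescue antiplatelet | Yes | Yes |
| Normal start, before day 30, rescue anticoagulant alone | No | No |
| Normal start, after antiplatelet start at day 30 | Yes | Yes |

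Under the wording in the Abstract and Study design, every row counts. The two wordings give different endpoints. The third and fifth rows are the difference, and both lie in the control arm.

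**2. Inputs for size**

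The plan gives no figure for rescue use or for re-hemorrhage, so there is none to reproduce on this point. From the Sample size section: 125 per arm, control rate 10.8%, and a 5% reduction read as absolute, giving 5.8%. These rates serve only as a planning scenario. They do not reproduce the stated total of 244: the usual two-proportion formula, two-sided 0.05 and 80% power, gives 477 per arm, 954 in all. That is a separate matter.

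Assumptions not in the documents: every MACCPE patient is rescued; rescue adds a re-hemorrhage risk *r* of 5% to 30%, the same in both arms; the underlying re-hemorrhage rate is 5% or 10%.

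**3. Rescue bleeds, if all bleeds are counted**

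- Rescued: control 125 × 0.108 = 13.5; early start 125 × 0.058 = 7.25; excess 6.25.
- Added bleeds, control: 13.5 × 0.05 = 0.7 to 13.5 × 0.30 = 4.1.
- Added bleeds, early start: 7.25 × 0.05 = 0.4 to 7.25 × 0.30 = 2.2.
- Shift in the between-arm difference: (0.108 − 0.058) × *r* = 0.25 to 1.5 percentage points.
- At an assumed 20% versus 10% MACCPE: excess 12.5 patients, shift 0.10 × *r* = 0.5 to 3.0 points.
- If *r* differs by arm, the shift is 0.108 × *r*(control) − 0.058 × *r*(early). It is zero when *r*(early)/*r*(control) = 10.8/5.8 = 1.86, and reverses above that.

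**4. Dependence on rescue class, under the literal definition**

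The 0.7 to 4.1 added control bleeds all count if rescue is antiplatelet, and none count if it is anticoagulant alone. Divided by 125, the control incidence can swing by 0.54 to 3.24 points. This is an upper bound, because it supposes a single class for all 13.5 patients and all such bleeds before day 30.

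**5. Untreated controls, under the literal definition**

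About 125 − 13.5 = 111.5 controls would have no antiplatelet for 30 − 3 = 27 days. If a fraction *f* of control bleeds falls in that period, the definition drops *f* × 5 or *f* × 10 points from the control rate at the two assumed underlying rates. This exceeds the 1.5-point shift of step 3 once *f* is above 1.5/5 = 30% or 1.5/10 = 15%. It acts in the opposite direction, because it removes control bleeds.

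**6. Precision**

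The 95% half-width for a difference at 125 per arm is 1.96 × √(2p(1 − p)/125): ±5.4 points at p = 5% and ±7.4 points at p = 10%.

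**The case against.** A reader might infer that rescue will fall mainly on controls and that early aspirin will therefore look safer than it is. The documents do not support that.

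- Rescue is unbalanced only if early aspirin lowers MACCPE, which is the hypothesis under test.
- Rescue in the early arm is added to aspirin and may carry more risk per patient. A ratio of 1.86 removes or reverses the effect.
- The literal endpoint wording omits bleeds in untreated controls, which makes early aspirin look less safe.
- The trial compares start times. Analysed by allocated arm, a control's bleed on rescue is a real consequence of the later start and belongs in the count.

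All four points stand. It is also fair to say that the shift from rescue bleeds is well inside the interval that 125 per arm can give, so an aspirin excess of that size would go undetected whatever was done about rescue. The remark that controls receive no antiplatelet may refer only to the first 30 days.

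It can further be said that the recorded data would let an analyst sort this out, and that a split by rescue belongs in an analysis plan that is not shown. That holds for the split. It does not hold for the endpoint definition: the article fixes a counting window, and that window conflicts with its own rescue rule and with its own shorter statements of the endpoint.

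**Conclusion.** The point holds as a defect of definition. The treatment condition in the safety endpoint gives the arms different counting windows and makes the control count depend on the class of rescue drug. It disagrees with the unconditional endpoint in the Abstract and Study design. The statements that controls receive no antithrombotic before day 30, and no antiplatelet, must also be reconciled with the rescue rule.

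No direction of bias can be claimed. The part due to rescue bleeds alone is small: 0.25 to 1.5 points, on the assumptions of 10.8% versus 5.8% MACCPE, rescue of every MACCPE patient, and an equal added risk of 5% to 30% in both arms. The loss of untreated-control bleeds could be larger and opposite in sign, but the documents give no re-hemorrhage rate or timing from which to size it. The correction is worth making because it is nearly free and the safety conclusion rests on this count.

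**What to change.** 1. Define the safety endpoint as any intracranial re-hemorrhage (the bleeding types already listed) from randomisation to day 90 in both arms, analysed by allocated arm and regardless of any antithrombotic received. Use the same wording in the Abstract, Study design and Endpoints sections.
2. Reconcile the statements on control-arm treatment in Step 2 and in the platelet-function section with the rescue rule in Step 3. Which clinical rule applies is for the investigators to state.
3. Tabulate rescue by arm, with drug class and start date, and report bleeds before and after first rescue as a descriptive sensitivity analysis. It should not be a second condition for the safety claim. Stopping follow-up at rescue conditions on a post-randomisation event that may itself differ by arm, and no margin is set for such a test.
4. Check that the case report form captures rescue class and start date, and that bleeds are recorded whether or not they are thought related to aspirin. The event list already asks for the time and special treatment of MACCPE and for the time, treatment and cause of bleeds.

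Cost: a sentence in the definition, a consistency edit and one extra table. The small downside is that the pre-rescue split must be read with the caution in item 3.

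### When uploaded 90-day examinations are inadequate and nothing more can be obtained, the whole patient is classed as withdrawn, although the plan's own phone review can still supply survival, function and reported events

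*Protocol article*

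**What the plan says.** Step 3: Outcome evaluation in the protocol article covers patients who cannot complete the 90-day examination at a participating centre: "they will be required to complete the relative examinations in the local hospitals". The next step reads: "Our investigators will ask patients’ family members to upload the follow-up data and assess the quality of these data". The consequence is then fixed. When the upload falls short in quality and nothing further can be obtained, "the patients will be considered as the patients withdrawing from the follow-up". Two conditions must both hold: inadequate quality, and no further details obtainable.

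The same article sets up other routes to 90-day information:

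- Table 2 (Procedure and data collection) lists, under outpatient or phone review, "Rebleeding event, MACCPE, survival condition".
- Table 3 schedules that review, and the clinic score, at the 90-day visit.
- Step 3 lets the clinic score of discharged patients be taken at an outpatient visit or by phone.
- Endpoints and relative definitions lists "the 3-month mortality after surgery" and 30- and 90-day mRS or GOS among the outcomes.

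Study design describes the trial as open-label with blinded endpoint assessment. Endpoints and relative definitions assigns two blinded investigators to assess MACCPE and re-hemorrhage. Step 3 does not say whether the investigators who judge upload quality are these two.

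**The concern.** A poor local scan or ultrasound is a problem with one set of examinations. The rule turns it into a change in the status of the patient, who may be alive, reachable and still consenting. Applied as written, it can end follow-up just when the phone review could still obtain vital status, mRS/GOS and a history of events. Data not collected at 90 days may not be recoverable at the analysis stage.

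Two features make this more than untidy wording. First, the patients affected are those who could not return to a study centre. The reason may be disability or simply distance; the article does not say. If disability plays a part, the loss depends on the outcome. Second, the quality decision determines who has 90-day data, and no blinding is stated for it. If allocation were known to those deciding, the loss could differ between arms.

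**Working it through.** **The plan's own figures.** The rule carries no number, so there is no figure of its own to reproduce. The check is mainly a comparison of passages.

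**Which 90-day outcomes need a readable local examination?**

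| Outcome at 90 days | Needs local imaging or laboratory data? | Other route in the article |
|---|---|---|
| Survival status | No | Outpatient or phone review (Tables 2 and 3) |
| mRS/GOS | No | Clinic score by phone for discharged patients (Step 3); scheduled at 90 days (Table 3) |
| Clinically reported MACCPE or rebleeding | Not for the report; confirmation may | Outpatient or phone review (Tables 2 and 3) |
| Silent infarct, silent deep venous thrombosis, silent re-hemorrhage | Yes | None at 90 days; earlier examinations only |

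Only the last row is necessarily lost when the upload is unusable. The rule nevertheless acts on all four.

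**Which data appear safe?** Step 3 says that patients with an ischemic event have met the endpoint and stay in the study. The list of events recorded during observation, which follows Figure 2, includes time of occurrence for MACCPE, death and intracranial bleeding. The special examinations at 10 ± 4 days and the clinic scores at 30 days precede the rule. No passage says that any of these are discarded. The statement that patients stay in covers ischemic events; there is no matching statement for re-hemorrhage.

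**Room for loss (Sample size section).** Planned enrolment minus stated need: 250 − 244 = 6 patients; 6/250 = 2.4%. No dropout rate is given. Under assumed losses of 5%, 10% and 20%, the evaluable number is 250 × 0.95 = 237.5, 250 × 0.90 = 225 and 250 × 0.80 = 200. The 244 is taken here as stated. As a separate matter, it does not follow from 10.8% versus 5.8% at 80% power and two-sided 5%, which gives 477 per arm (954 in total).

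**Sensitivity to a few lost events.** Inputs are 125 per arm and a 10.8% rate (Sample size section). Expected events at that rate: 125 × 0.108 = 13.5 per arm; at 5.8%: 125 × 0.058 = 7.25. Suppose the true rate is 10.8% in both arms and m event patients drop out of one arm only. The observed rate there is (13.5 − m)/(125 − m):

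- m = 3: 10.5/122 = 8.6%, a difference of 2.2 points;
- m = 6: 7.5/119 = 6.3%, a difference of 4.5 points.

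These lines show only that event counts are small. The values of m are assumptions, and for MACCPE they could apply only to events not already recorded.

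**The case against.** The strongest reply is that the rule is close to ordinary loss to follow-up. It applies only when further details cannot be obtained, and the 90-day phone review is an obvious source of such details. On that reading, few reachable patients would be caught. This narrows the trigger but does not remove the problem: details most naturally refers to the uploaded examinations, and the consequence still falls on the whole patient.

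A reader might infer three stronger things that the documents do not support.

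- *That the rule creates a spurious MACCPE benefit of some 2 points.* This would require event patients to be removed unequally. Step 3 appears to keep patients with recorded ischemic events. The Introduction places most events within one month, and the Discussion puts the peak at day 7, so few MACCPE should depend on the day-90 examination alone.
- *That earlier or phone data are thrown away.* Withdrawing from follow-up may simply mean that follow-up ends there.
- *That unblinded staff decide who is missing.* The article also calls the blinded assessors investigators, and Step 3 is silent on who knows allocation.

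Two further points stand in part. The analysis may censor such patients: Cox regression is named, although the main text ties it to an undefined PR analysis, and the subgroup section applies Cox models to the efficacy and safety endpoints. That choice can be left to an analysis plan, but censoring does not cure outcome-dependent loss, nor does it help the mRS comparison. Also, an uploaded examination shows that the patient was alive on its date, so the rule is not a major route for losing deaths; it mainly leaves formal 90-day status open.

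**Conclusion.** The concern holds in a limited form. The article states a patient-level withdrawal rule for what is an examination-level defect, and this conflicts with the 90-day phone routes in its own Tables 2 and 3 and Step 3. It also leaves the quality judgement without stated blinding in an open-label trial. The exposed outcomes are mainly 90-day mRS/GOS, 90-day survival status, later re-hemorrhage and late MACCPE.

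The size and direction of any bias cannot be derived from the documents. They give neither the number of patients who will use local hospitals, nor the proportion of uploads that will fail, nor the reasons for not returning. The documents do show little slack: a margin of 6 patients (2.4%) over the stated need and about 13.5 expected control events. The conclusion rests on reading the sentence as written. Figure 2 and the full protocol, neither shown, may give operational detail that softens it.

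**What to change.** Replace the sentence in Step 3 with a rule to this effect:

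- If locally obtained 90-day examinations cannot be assessed and no further details are available, only the affected examination component is missing for that visit.
- The patient remains in follow-up. Survival, mRS/GOS and reported MACCPE and rebleeding are taken from the 90-day outpatient or phone review.
- All earlier events and assessments, and the phone-obtained data, are retained in the analysis.
- The two blinded assessors named in Endpoints and relative definitions judge the quality of uploaded data without knowledge of allocation.
- The term withdrawn is reserved for withdrawal of consent.

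The cost is almost entirely wording, since the phone review and the blinded assessors are already planned. The assessors gain a small extra task, and uploads must reach them without allocation information. The real downside is that some late silent events would rest on earlier imaging and clinical report, without a readable 90-day examination.
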